## Abstract

**Background:**

One out of five patients is unsatisfied to some extent after total knee arthroplasty (TKA). Unmet expectations are the main driver of post-operative dissatisfaction. Improved pre-operative education on realistic expectations for long-term outcome after TKA potentially leads to higher post-operative satisfaction. The effect of expectation modification on post-operative satisfaction in TKA patients has not yet been studied. The primary objective of the presented study is to examine whether an educational module on long-term recovery after TKA will improve patient satisfaction compared to usual pre-operative education.

**Methods:**

The EKSPECT study is a randomized controlled trial. Patients with symptomatic and radiographic knee osteoarthritis who are indicated for a primary TKA will be randomized to the usual pre-operative education (control group) or usual education plus an additional module on realistic expectations for long-term recovery (intervention group). Patients will be naïve to study objective and difference between study groups. Outcome expectations will be measured blinded for group allocation using the HSS Knee Replacement Expectations Survey at baseline (before the intervention), pre-operatively (after the intervention) and fulfillment of expectations at 12-month follow-up. Baseline physical function, quality of life and psychological factors are measured using self-reported questionnaires. The primary outcome measure is satisfaction with treatment result at the 12-month follow-up.

**Discussion:**

The EKSPECT study should provide evidence on the effectiveness of an education module on long-term recovery after TKA to improve treatment satisfaction. If beneficial, the education module is a simple intervention with a low burden for patients, which can easily be implemented in clinical practice.

**Trial registration:**

Dutch Trial Registry registration number: NTR5779. Registered on 17 March 2016.

**Electronic supplementary material:**

The online version of this article (10.1186/s13063-018-2821-2) contains supplementary material, which is available to authorized users.

## Background

Total knee arthroplasty (TKA) is a frequently performed procedure for patients with knee osteoarthritis. The Dutch arthroplasty registry reported an increase from 20,573 TKAs in 2010, to 27,107 in 2016 in the Netherlands [1]. A further increase in these numbers is expected in the future due to aging of the Western population and the growing number of overweight people [1].

TKA is considered an effective intervention for end-stage knee osteoarthritis. Considerable pain reduction, increase in physical function and quality of life can be achieved [2, 3]. The treatment is relatively safe, cost-effective and excellent survival rates are reported, with prosthesis survival of more than 95% at 15 years’ follow-up [2, 4]. Despite these favorable figures, the rate of satisfaction after TKA is consistently reported to be around 80%, leaving one in five patients unsatisfied to some extent after their knee surgery [5, 6].

Patients have multiple expectations regarding the outcome of TKA, mainly concerning relief of pain, improvement in physical functioning and improvement in psychosocial wellbeing [7, 8]. Pre-operative expectations tend to be high, and are often overly optimistic [9, 10]. Frequently, a discrepancy exists between expectations of the patients and those of the surgeon [11], and a substantial number of patients are reported to have unfulfilled expectations after TKA [12]. The fulfillment of pre-operative expectations on treatment outcome is reported as the main determinant of treatment satisfaction after TKA [5, 6, 13, 14]. Patients with unfulfilled expectations, are up to 10 times more likely to be dissatisfied with their treatment results [13, 14]. These findings suggest that more realistic expectations potentially lead to higher post-operative satisfaction.

The current pre-operative patient education is predominantly focused on the process of care and the immediate post-operative period. Previous research has shown that structured pre-operative education on realistic expectations for long-term recovery can alter pre-operative expectations [15]. After such an intervention, expectations of patients are reported to be lower and the rate of discordance between patients’ and surgeons’ expectations is reduced [11, 15]. These findings suggest that specific education about post-operative outcome could lead to more realistic patient expectations. The effect of pre-operative expectation management on post-operative expectation fulfillment, and ultimately better post-operative satisfaction after TKA, has not yet been studied.

## Trial objectives

The primary objective of this randomized controlled trial is to examine whether an additional education module on realistic expectations for long-term recovery of symptoms, physical functioning and psychological issues (intervention group) will improve patient satisfaction after TKA compared to usual pre-operative education (control group).

Furthermore, an analysis will be made to determine if the additional education module on pre-operative expectations of TKA patients leads to change in pre-operative outcome expectations and an increase in post-operative expectation fulfillment. An analysis will be made on the relationship between expectation fulfillment and treatment satisfaction. Additionally, an explorative analysis will be performed on the effect of the additional education module in subgroups of patients, depending on age, gender, severity of symptoms, symptoms of depression, coping mechanisms and degree of pre-operative expectations.

## Methods

### Study design

The influence of Expectation modification in Knee arthroplasty on Satisfaction of PatiEnts, a randomized Controlled Trial (EKSPECT) study is a randomized, clinical superiority trial, with a parallel-group design and 1:1 allocation ratio. Patients will be randomized to group (a) usual education plus an additional module on realistic expectations for long-term recovery, or in group (b) usual education. Patients will be naïve to study objective and difference between study groups. Measurements will be performed blinded for group allocation at baseline, on day of admission and 12 months after TKA procedure. A flow chart of the study procedures can be found in Fig. 1. The study has been reviewed and approved by the Máxima Medical Center Medical Ethics Committee (registration code NL54671.015.15). The study has been registered in the Dutch Trial Registry (registration number NTR5779) and has not been amended. If protocol amendments are conducted, these will be updated on the Trial Registry record. A Standard Protocol Items: Recommendations for Interventional Trials (SPIRIT) Checklist on the study protocol is provided as Additional file 1.

**Fig. 1 Fig1:**
[figure not shown]
EKSPECT study Consolidated Standards of Reporting Trials (CONSORT)-style flow diagram

### Setting

The study will be conducted at the Department of Orthopedic Surgery and Trauma of the Máxima Medical Center. This is a large, non-academic teaching hospital where approximately 350 primary TKAs are performed annually. In total, five experienced orthopedic surgeons perform these procedures.

### Study population

Patients eligible for this trial are patients presenting at the Outpatient Clinic of the Department of Orthopedic Surgery at the Máxima Medical Center, with clinical and radiological knee osteoarthritis, indicated and scheduled for a TKA. The indication for a TKA is set according to the guideline of the Dutch Orthopedic Society [16]. This guideline recommends considering TKA only in patients with radiological knee OA of Kellgren and Lawrence grade ≥ 2 and pain and functional impairment with influence on quality of life, work and/or social life [16].

#### Inclusion criteria

In order to be eligible to participate in this study, a subject must meet the following criterion:Symptomatic and radiographic knee osteoarthritis indicated for a primary TKA

#### Exclusion criteria

A potential subject who meets any of the following criteria will be excluded from participation in this study:Presence of a medical illness that results in a life expectancy shorter than 1 yearPresence of TKA of the contralateral sideUnicompartmental knee arthroplastyStaged or bilateral knee arthroplastyInsufficient command of the Dutch languageLegally incompetent adults

The exclusion criteria were chosen because the primary outcome will be measured at the 1-year follow-up and sufficient proficiency of the Dutch language is necessary for understanding of the intervention under study and the completion of patient-reported outcome measures. Furthermore, patients who already have a TKA on the contralateral side will be excluded because their personal experience with knee arthroplasty is known to result in considerable bias on the expectations of outcome after TKA [17]. Patients in whom at baseline it is already evident that they will undergo TKA during the study period (either bilateral or staged) are excluded. These patients are excluded because contralateral knee arthroplasty during the study period is likely to influence satisfaction and functional outcome scores of the index knee as well.

### Recruitment

After being indicated for TKA by their orthopedic surgeon and placed on the waiting list for surgery, eligible patients for the study will be screened by a research nurse. When inclusion and exclusion criteria are met, the patient will be asked to participate in the study. Written information on the study objective and procedures will be provided, and patients will have the possibility to ask additional questions when necessary. The patient will be informed that two education modules are compared in this study, but the difference between the usual care and intervention module is not specified. During this process, patients are blinded for the hypothesis of the study to avoid bias and patient preference for one of the two modules. If a patient is willing to participate, an informed consent form will be signed and baseline measurements registered.

### Randomization

The randomization procedure will be performed after the patient is cleared for surgery in pre-operative screening by the anesthesiologist, and a definitive date for surgery has been determined. Allocation to type of intervention takes place by receiving the consecutive randomization number from the coordinating investigator. A computer-generated randomization list will be used (Research Manager version 5.30.0.6, Cloud9 Software, Deventer, The Netherlands). Patients will be included by each of the five orthopedic surgeons performing and indicating patients for TKA. Because information on outcome after TKA provided by each orthopedic surgeon during the consultation might be different on details, block randomization with variable size of blocks, stratified for orthopedic surgeon is used. This accounts for potential information bias in this regard. All clinical and trial staff will be blinded for allocation during the study procedure. Patients were invited for a specific education class by mail to avoid cross-over, and only the secretary sending the invitation letters for the education sessions is unblinded. Attendance of the education class in the intervention and control arms is recorded blinded using the data management software. Data analysis will be obtained and analyzed blinded for group allocation. Only after data analysis will unblinding take place.

### Intervention

#### Theoretical framework / rationale for using an education module to increase post-operative satisfaction

Patient expectations have been defined as “anticipations that given events are likely to occur during or as a result of medical care,” and expectations regarding treatment result are defined as “outcome expectations” [18–21]. The present study addresses probabilistic outcome expectations; what does the patient think is the most likely long-term result after TKA? [18–20].

Different hypotheses on the effect of expectation modification on treatment outcome and satisfaction have been suggested. In general, positive expectation of recovery has shown to be associated with better health outcomes [22, 23] and lower recovery expectations increased the risk of persistent activity limitations [24]. The strength of the relation depends on the clinical conditions and the method of expectation measurement used [22]. Expectations that are too low or negative can result in less motivation to obtain full benefit from the surgery, and increasing patient expectations is suggested to improve treatment outcome [25, 26]. Suggested explanations for this positive effect are that higher expectations result in anxiety reduction, better cooperation with treatment and beneficial coping mechanisms [27, 28]. There is evidence that expectations are a mechanism by which placebos have their effects [25]. Utilization of this placebo effect as an intervention to obtain positive health-related effects has been shown in laboratory settings with predominantly healthy volunteers, [28] but these positive results have not been consistently reproduced in clinical research [29]. To the authors’ knowledge there are no intervention studies available on the effect of increasing expectations to improve treatment outcome in TKA patients. So, it remains to be seen if this potential positive effect actually occurs and to what extent outcome improvement can be obtained.

On the other hand, unrealistically high expectations can result in discouraged patients and non-adherence with recommendations post-operatively. Total knee arthroplasty patients often have overly optimistic pre-operative expectations when compared to surgeons [11] and when compared to actual outcome [9, 30]. Furthermore unmet pre-operative expectations are strongly related to post-operative dissatisfaction [5, 6]. These findings are in line with the expectancy-disconfirmation theory, which states that satisfaction is a function of expectations, perceived performance and disconfirmation of beliefs [31]. Therefore, in the authors’ opinion an education module should not result in overly optimistic expectations, as these pose the risk of expectation disconfirmation with subsequent patient dissatisfaction.

In conclusion, expectation management in knee arthroplasty patients is thought to have an effect on post-operative satisfaction and outcome through various pathways. Whereas, on the one hand, expectations should be high enough to fully benefit from the placebo effect, on the other hand, unmet expectations can result in higher dissatisfaction rates after treatment. “Optimistic realism” is suggested as the appropriate balance between preventing dissatisfaction and optimizing context effects [32]. In the authors’ view both aspects are important, and it is key to identify the patients with unrealistic expectations; either too high or too low and adjust these accordingly. Therefore, the aim of the proposed additional education module is to achieve realistic expectations on long-term recovery after TKA.

#### Intervention arm

The intervention under study is a joint-specific educational module on long-term recovery after TKA (12 months post-operative). The additional education module is an extension to the pre-operative education program as described for the control group. Information in the education module is based on an academic literature study, the expert opinion of TKA surgeons in our own clinic and a survey among members of the Dutch Knee Arthroplasty Society [33]. The final module was written and approved by an expert panel consisting of an experienced knee surgeon (RJ), an orthopedic surgery resident and PhD student (JT) and a researcher specialized in osteoarthritis treatment outcome (MR).

Previous research has identified a set of important expectations that are often not fulfilled in TKA patients [7, 8, 30]. These items are incorporated in the Hospital for Special Surgery (HSS) Knee Replacement Expectations Survey [7, 34]. Items addressed in this survey were used as the framework for the education module. The module describes what patients can generally expect 12 months post surgery concerning the amount of pain, functioning in daily life (e.g., walking, rising from a chair, stair climbing); performing social activities (e.g., hobbies, sport activities); and psychological wellbeing (e.g., psychological wellbeing, interactions with others). Information is provided for the most likely outcome for the whole population of TKA patients. Additionally, modifying factors are addressed that predict higher or lower outcome for an individual patient; age, medical co-morbidity, Body Mass Index (BMI), psychosocial factors, pain severity and pre-operative functional status [35, 36]. The module consists of a group-based lecture of approximately 15 min, given by the senior author (JT, orthopedic surgery resident and PhD student), and information on realistic outcome expectations after TKA in writing (Additional file 2). When patients have additional questions or concerns regarding realistic expectations on treatment outcome, these will be addressed after the lecture. The module was formatted into the existing standard program with a session once a month for approximately five to 10 patients, and is in concordance with recommendations on education class structure [37].

In summary, the education module states the following: overall good effect for long-term recovery after TKA can be expected [33]. Most improvement can be expected for the items pain relief, ability to perform daily activities and walking short to medium distances [10, 33, 38]. Significant pain relief is achieved in most patients after TKA, nevertheless, some residual pain is common [10, 38]. Impairment in daily activities is likely to decrease. At 12 months much better or better activity of daily living function is reported by more than 90% of patients, only 4–8% of patients report some problems in daily living [10, 39]. A large improvement or return to normal can be expected on walking short and medium distances [10, 33, 40]. For longer distances, some limitations are likely to remain [10, 33]. Least improvement can be expected for the activities of kneeling, squatting, stair negotiation and the ability to exercise or participate in sports [33, 38]. Approximately 80% of patients report to be unable to kneel or squat without knee symptoms after TKA [41, 42]. The rate of return to sport is dependent on patient characteristics and type of sports. The intensity of activity to which patients return tends to be less than before surgery; 94% are able to do low-impact sports but only 43% are reported to return to high-impact sports [43, 44].

The above summary is not exhaustive, but in the actual education module realistic expectations for all items of the HSS Knee Replacement Survey are addressed. Improvement can be expected in the domains of pain, function, activities and psychological wellbeing but return to normal is not likely to occur. Limitations can predominantly be expected in more demanding physical activities and sports.

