#### Control arm

The standard pre-operative education program consists of information about the perioperative period, but does not include information on long-term recovery. The admission process, details about the anesthesia process, surgical technique, complications, pain management, the direct post-operative recovery and rehabilitation during the first 6 weeks post-operative are addressed. During a 120-min multidisciplinary pre-operative class an anesthesiology assistant, physiotherapist, orthopedic nurse and orthopedic surgeon teach a 30-min module each. The information is summarized in a brochure for the patients. This education module currently is the standard care in Máxima Medical Center for all TKA patients.

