### Statistical analysis

The primary analysis will be performed according to intention-to-treat principles following the original group allocation regardless of the intervention that they actually received. Missing data will be accounted for by a multiple imputation technique. A secondary per-protocol analysis will be performed, including only those patients who completed the treatment originally allocated. Reasons for cross-over will be explored. Distribution of all variables will be tested by the Shapiro-Wilk test. For the normally distributed variables, parametric tests will be used. For the variables that were not normally distributed non-parametric tests will be used.

The primary outcome will be analyzed by using logistic regression analyses (patient satisfaction with the 12 months’ results of TKA as dependent and intervention as independent variable), variables of which a priori are known to be associated with patient satisfaction, based on previous studies or based on a strong clinical rationale, will be considered as covariates in the primary analysis. These covariates are age, gender, BMI and baseline expectations as assessed by the HSS Knee Replacement Survey, anxiety, depression. The assumptions of constant variance and linear relationships will be assessed using scatter plots. Should any of these assumptions seriously fail, then transformation of the dependent or independent variable(s) (where applicable) will be used. The choice of which transformation (e.g., square root, logarithm) will be used based on the specific distribution of the residuals. Similar analyses will be performed for the secondary outcome parameters. Change in outcome expectations before and after pre-operative education (baseline vs pre-operative), and difference between intervention and control group in change in baseline and pre-operative expectations will be analyzed using linear regression analyses. Statistical calculations will be made using IBM® SPPS software, version 19.0.

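### Both arms are taught in group classes, but the stated models and sample size treat patients as independent; if outcomes correlate within sessions, standard errors will be too small

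*Protocol article*

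**What the plan says.** **Delivery.** Under Intervention arm, the module is an addition to the usual education: "The module consists of a group-based lecture of approximately 15 min", given by one lecturer, with written information and time for questions afterwards. It runs "with a session once a month for approximately five to 10 patients". Under Control arm, the usual education is also taught in a class: "During a 120-min multidisciplinary pre-operative class an anesthesiology assistant, physiotherapist, orthopedic nurse and orthopedic surgeon teach a 30-min module each". The size of that class is not given.

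**Allocation.** Under Study design, the trial is described as "with a parallel-group design and 1:1 allocation ratio". Under Randomization, "block randomization with variable size of blocks, stratified for orthopedic surgeon is used", and "Patients were invited for a specific education class by mail to avoid cross-over". I read the last statement as meaning that each class holds patients of one arm only.

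**Analysis.** Under Statistical analysis, "The primary outcome will be analyzed by using logistic regression analyses", with intervention as the independent variable. The covariate list is closed: "These covariates are age, gender, BMI and baseline expectations as assessed by the HSS Knee Replacement Survey, anxiety, depression". Secondary outcomes are to be analysed similarly, and change in expectations by linear regression. No session term, random effect or cluster-robust error is named. The Sample size section asks for 90 per group and mentions neither an ICC nor a design effect.

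**The concern.** Patients in one session hear the same questions and answers and can influence one another. That can make their later answers more alike than those of patients from different sessions. Because each session belongs to one arm, variation between sessions does not cancel in the comparison of arms; it adds to the variance of the treatment effect. Ordinary logistic or linear regression does not count this part. Confidence intervals would then be too narrow, the true type I error would exceed 5%, and a correctly analysed trial would have less power than stated.

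Expectations are measured at admission, after the class, and they are the step through which the module is meant to work. Session effects are most plausible there. They are less plausible for satisfaction with the operation 12 months later.

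**Working it through.** **1. The plan's own sample size.** Inputs from the Sample size section: 50% against 70% very satisfied, alpha 0.05 (taken as two-sided), power 80%. With the unpooled normal approximation:

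n = (0.50×0.50 + 0.70×0.30) × (1.960 + 0.842)² / 0.20² = 90.3 per group.

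This matches the stated 90, so the calculation is one for independent patients (design effect 1). Power at 90 per group is 79.9% by the same formula. The dropout step hides no allowance for clustering: the final 204 is below 180/0.85 = 212.

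**2. Patients per session.** The article gives about 5 to 10 patients per session. Trial patients per session could be fewer. The Trial status section has inclusion starting in summer 2016 and results in mid-2019. With 12 months of follow-up, this leaves roughly 20 to 24 monthly sessions (an inference). With 204/2 = 102 patients per arm, that is 102/24 = 4.25 to 102/20 = 5.1 per session. I therefore use m = 4 to 10, and apply it to the control class as an assumption.

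**3. Formulas.**
- Design effect: DE = 1 + (m − 1) × ICC.
- Variance ratio under the null: v = DE if both arms cluster; v = (1 + DE)/2 if only intervention sessions do.
- Type I error of the unadjusted test: 2 × [1 − Φ(1.96/√v)].
- Power at 90 per group with the correct standard error: Φ(0.20/SE − 1.96), where SE² = (0.21×DE₁ + 0.25×DE₀)/90. DE₁ and DE₀ are the design effects in the intervention and control arms, with DE₀ = 1 if only intervention sessions cluster.

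**4. Results.** The ICC values are assumptions. Ranges run from m = 4 to m = 10.

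| ICC | DE | Type I error, intervention only | Type I error, both arms | Power, intervention only | Power, both arms |
|---|---|---|---|---|---|
| 0 | 1 | 5.0% | 5.0% | 80% | 80% |
| 0.01 | 1.03–1.09 | 5.2–5.5% | 5.3–6.1% | 79–78% | 79–76% |
| 0.02 | 1.06–1.18 | 5.3–6.1% | 5.7–7.1% | 79–77% | 78–73% |
| 0.05 | 1.15–1.45 | 5.9–7.7% | 6.8–10.4% | 77–72% | 74–64% |

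Worked example, ICC 0.05, m = 10, both arms: DE = 1 + 9 × 0.05 = 1.45. The true standard error is √1.45 = 1.20 times the reported one. Type I error = 2 × [1 − Φ(1.96/1.204)] = 10.4%.

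**5. Check by simulation.** A beta-binomial simulation (90 per arm, both arms clustered, unadjusted Wald test of the log odds ratio) gave these type I errors for m = 5 and m = 10:
- ICC 0: 4.4% and 4.6%
- ICC 0.01: 5.1% and 5.3%
- ICC 0.02: 5.4% and 6.5%
- ICC 0.05: 6.8% and 9.7%

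These are a little below the formula, partly because the unadjusted test is slightly conservative even at ICC 0. The pattern is the same.

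**The case against.** The tempting stronger reading is that the standard errors are too small, full stop. The article does not support this. Patients are randomised individually, so there is no inflation unless session membership affects outcomes, and no ICC is reported from which to conclude that it does.

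Several features point to a small ICC for the primary outcome: a lecture of about 15 minutes, common written information, and an individual rating made 12 months later. Two mechanisms that a reader might infer are also weak. One person gives the module lecture, so differences between lecturers cannot create variation between its sessions. Calendar period is largely balanced by concurrent, blocked 1:1 randomisation. Nor does the article say that the staff of the standard class rotate or differ by arm. What remains is shared questions and group interaction.

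The largest figures also need a large session, an ICC of 0.05 and clustering in both arms, although the control class size is unknown. All of this stands, and it limits the point to a conditional one.

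A further objection is that a full protocol or analysis plan, not shown, could add a clustered analysis, and that logistic regression does not exclude robust errors. This stands only in part. The article states the primary model, its covariates and the sample size, and none allows for session. A later choice of standard error would not restore the stated power.

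**Conclusion.** The point holds in conditional form. The stated analysis and sample size rest on independence within sessions, which the group delivery makes doubtful and the article does not justify. The consequence is nil at ICC 0, modest at 0.01 to 0.02, and material at 0.05. This rests on assumed ICCs, on 4 to 10 trial patients per session, on classes being separate by arm, and, for the both-arm figures, on control classes of similar size.

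The exposure is greatest for expectations at admission and smaller for satisfaction at 12 months. It does not show that the trial's result would be wrong. It is a worthwhile, inexpensive improvement to the plan.

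**What to change.** - Record a coded identifier for the assigned session of every patient in both arms. Use the assigned rather than the attended session, in keeping with intention to treat. Class attendance is already recorded, so this is one more field, but it may be hard to recover later.
- Pre-specify session-level clustering for the primary satisfaction model and for the model of expectations at admission: a random intercept for session, or cluster-robust standard errors. At minimum, make this a named sensitivity analysis reported beside the main result.
- With robust errors, use a small-sample correction. There would be roughly 90/10 = 9 to 102/4 ≈ 25 sessions per arm if control classes are of similar size.
- State the assumed ICC range and the resulting power at 90 per group.

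The cost is one data field, one model term and slightly wider confidence intervals. If the ICC is near zero, little is lost.
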